**Figure 1 figure1:**
[figure not shown]
Condition A and B timelines. GAD-7: 7-item Generalized Anxiety Disorder assessment; MAQ: Medication Adherence Questionnaire; PGIC: Patient Global Impression of Change questionnaire; PHQ-9: 9-item Patient Health Questionnaire; QOLIE-10-P: 10-item patient-weighted Quality of Life in Epilepsy questionnaire; T: time point.

Data will be collected at baseline (T0, plus T–1 for wait-list participants), T1 (4 weeks after commencement of the ThinkNinja for Epilepsy intervention), T2 (8 weeks after commencement of the intervention), and T3 (8 weeks following completion of the active period of the study) via participant-completed questionnaires.

The secondary outcomes include anxiety (GAD-7), depression (PHQ-9), patients’ global impression of change (PGIC), and self-reported medication adherence (MAQ). All measures to be collected at T–1, T0, T1, T2, T3, and weekly were chosen due to their suitability, reliability, validity, and established sensitivity to change for people with epilepsy and for evaluating changes in quality of life, anxiety, and depression levels. The measures chosen are also balanced with consideration to minimizing burden on both participants and researchers and maximizing data quality. All T–1, T0, T1, T2, T3, and weekly measures will be completed online and will be self-reported by the participants. In addition, demographic characteristics, including age, gender, and ethnicity, will be self-reported by participants at baseline [36].

At each time point, bespoke questions will also be included to cover any change in medications and any psychological support services the participant may have accessed during the study, such as services from their local NHS, including mental health services covering counseling or therapy. These will be self-reported by the participant. To minimize potential self-reporting inaccuracies, the participant will be asked to recall any additional support over the previous 3 months at T–1, T0, T1, T2, and T3, instead of recalling any additional support over the full study period at completion.

Other measures captured within the app at various frequencies via user input and app tracking mechanisms are as follows:

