### Data Analysis

The analysis will be performed in two phases. The first phase of analysis will occur after completion of the 8-week (T2) outcome measures, when all participants in arm A have completed the 8-week program and can be compared to the waiting-list control participants (arm B). The second phase of analysis with the pooled data will occur after the completion of the 8-week follow-up period (T3) outcome measures for all participants.

The following patient cohorts will be used in the analysis:

The per-protocol study cohort will include all allocated participants with at least 80% completed questionnaire data, including a completed QOLIE-10-P score, at baseline (T0 ThinkNinja for Epilepsy group and T–1 wait-list group) and at 8 weeks (T2 ThinkNinja for Epilepsy group and T0 wait-list group).The intention-to-treat study cohort will include all allocated participants.

Available information on screened participants who were not randomized will be summarized.

Descriptive statistics will be produced for the distribution of all variables, including baseline demographic variables, app use, and engagement variables, as well as for each outcome variable at each time point. The change in each outcome from baseline will be reported in terms of mean and SD. An analysis of reliable and clinical change will be produced for the GAD-7 and PHQ-9 scores in order to determine the percentage of those who had clinical and reliable change (ie, clinical recovery) after taking part in the intervention.

The primary outcome analysis (ie, quality of life) will be performed for the overall cohort, both unadjusted and adjusted for baseline characteristics, app use, and app content variables. We will be comparing changes in quality of life (ie, QOLIE-10-P scores) from baseline to completion of the 8-week program.

The secondary outcome analysis will constitute analyzing the change in GAD-7 (ie, anxiety) and PHQ-9 (ie, depression) scores. In addition, we will be reporting on the results of the MAQ and PGIC, using descriptive statistics.

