In addition to this, a sensitivity analysis that uses both the primary and secondary outcomes will be performed. To explore both between-subjects (ie, arm A vs arm B) and within-subject (ie, T0 vs T1 vs T2 vs T3) differences, a series of repeated-measures (2 × 4) analyses of variance (ANOVAs) will be performed in the first instance with both the primary outcome measure (ie, QOLIE-10-P score) and the secondary outcome measures (ie, GAD-7, PHQ-9, PGIC, and MAQ scores) as dependent variables. All of these ANOVA tests will be powered at 0.80 (*P*=.05). The output from this series of ANOVAs will permit the necessary sensitivity analyses to be completed.

Further exploratory subgroup analyses will be performed for the following:

Change in primary and secondary outcomes for subgroups defined by baseline characteristics and demographics, such as age and gender.Change in primary and secondary outcomes stratified by app use, videoconference use, and text support use.Engagement variables: low versus high frequency and duration of app use.

Responder and nonresponder groups will be identified on the basis of changes in primary and secondary outcomes, and these groups will be characterized in terms of baseline characteristics, demographics, and app use variables. Descriptive statistics will be produced, and a regression model will be performed to identify variables associated with responder status. An SEM model will then be developed where baseline characteristics will be independent variables, app use and content variables will be mediating latent variables, and quality of life will be the dependent variable. Regression coefficients will be reported with 95% CIs. These analyses will be performed as an intention-to-treat analysis, using all randomized participants with imputation of missing end-of-study (T2) observations, with the exception of the sensitivity analyses, which will be per-protocol analyses.

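### The 2 × 4 sensitivity ANOVA compares the arms over T0 to T3, counted from app start, so its arm terms do not estimate app versus waiting list, and its stated 0.80 power is not derived

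*Protocol article*

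**What the plan says.** All references are to the protocol article.

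- **Data Analysis, the ANOVA.** The stated purpose has two parts. The first reads "To explore both between-subjects (ie, arm A vs arm B"; the second reads "within-subject (ie, T0 vs T1 vs T2 vs T3) differences, a series of repeated-measures" (2 × 4) ANOVAs. The dependent variables are QOLIE-10-P, GAD-7, PHQ-9, PGIC and MAQ. The section calls this a sensitivity analysis and assigns it to the per-protocol cohort.
- **Data Analysis, power.** "All of these ANOVA tests will be powered at 0.80", at a significance level of .05.
- **Outcomes and Variables, text below Figure 1.** Baseline is "T0, plus T–1 for wait-list participants". The next visit is "T1 (4 weeks after commencement of the ThinkNinja for Epilepsy intervention". T2 is 8 weeks after app start, and T3 is 8 weeks after the active period ends.
- **Study Procedure and Limitations.** Arm B gets the same full app access after 8 weeks, and its T0 is taken as it moves onto the app.
- **Data Analysis, per-protocol cohort.** Baseline is T0 in arm A and T–1 in arm B. The 8-week visit is "T2 ThinkNinja for Epilepsy group and T0 wait-list group".
- **Sample Size.** Two-sided two-group t test, alpha .05, 80% power, d=0.5, based on QOLIE-10-P; 92 per arm, allowing 30% dropout. The only other power figure is for the structural equation model.

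**The concern.** The same visit label means different things in the two arms once time is counted from randomisation. The per-protocol cohort definition allows for this; the ANOVA does not. Crossing arm with T0 to T3 sets arm A on its app course against arm B on its own app course, and the waiting period drops out of the model.

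The between-arm half of the analysis then does not address its stated question for any of the five outcomes. For MAQ and PGIC the article otherwise plans only descriptive statistics, so this ANOVA is their only named test between arms. A null interaction reported beside a claim of 80% power could be read as evidence against the app, or as contradicting a positive primary result. A significant arm term could be read as a benefit when it reflects change during the wait.

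**Working it through.** **1. Reproduce the plan's own figure.** Two-sample t test, d=0.5, two-sided alpha .05, power 0.80: n = 63.77, so 64 per arm (power at 64 is 0.801). Dropout 30%: 64 / 0.70 = 91.4, so 92 per arm and 184 in total. This matches exactly.

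**2. Visits in weeks since randomisation**

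| Visit | Arm A | Arm B |
|---|---|---|
| T–1 | none | 0 |
| T0 | 0 | 8 |
| T1 | 4 | 12 |
| T2 | 8 | 16 |
| T3 | 16 | 24 |

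The arms share only weeks 0, 8 and 16, so aligning by calendar time cannot produce four common levels either. At week 16 both arms have had the app. Arm B's total is 8 (wait) + 8 (active) + 8 (follow-up) = 24 weeks, whereas the Results section gives 16.

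**3. What the arm terms estimate.** Let m be the common mean at randomisation, w arm B's change during the wait, and a1, a2, a3 and b1, b2, b3 the changes from app start to T1, T2, T3 in arms A and B.

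- Arm A means: m, m+a1, m+a2, m+a3.
- Arm B means: m+w, m+w+b1, m+w+b2, m+w+b3.
- Arm-by-time contrasts: a1−b1, a2−b2, a3−b3.
- Arm contrast (average over four visits): −w + [(a1−b1)+(a2−b2)+(a3−b3)]/4.
- App versus waiting at week 8: a2 − w.

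With equal app effects (each a equal to its b), the interaction is zero and the arm contrast is −w. Neither contains a2.

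**4. Simulated size.** Assumptions not in the article: 64 per arm, SD 1, compound symmetry with correlation 0.3, 0.5 or 0.7, on-app course 0, 0.25, 0.5, 0.5 SD in both arms, 4,000 runs per scenario.

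| Scenario | Arm | Arm-by-time | Time |
|---|---|---|---|
| No change during wait | about 0.05 | about 0.05 | above 0.99 |
| 0.2 SD drift during wait, either direction | 0.24 to 0.38 | about 0.05 | above 0.99 |

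Analytic check of the drift row: the SD of a four-visit mean is √((1+3ρ)/4), which is 0.689, 0.791 and 0.880 at ρ = 0.3, 0.5 and 0.7. The standardised difference is 0.2 divided by these, giving power of about 0.38, 0.30 and 0.25.

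**5. Power on the randomised window** (arm A T0, T2; arm B T–1, T0), d=0.5, 64 per arm:

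| ρ, baseline to week 8 | Arm-by-time, d/√(2(1−ρ)) | ANCOVA, d/√(1−ρ²) |
|---|---|---|
| 0.3 | 0.66 | 0.84 |
| 0.5 | 0.80 | 0.90 |
| 0.7 | 0.95 | 0.98 |

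Even on the right window, 0.80 is not automatic: an arm-by-time or change-score test reaches it only if the correlation is about 0.5 or more.

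**The case against.** The trial is exploratory and this is a per-protocol sensitivity analysis. The cohort definition in the same section already holds the right window, and the first analysis phase compares arm A at 8 weeks with the waiting list. That stands, and it limits the severity.

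The ANOVA also has a within-subject purpose, for which visits aligned to app start are the natural layout. This stands too. A reader might infer that the model can detect no effect of any kind; the documents do not support that, because the time term picks up pre-post change readily, though without a control. The arm term could likewise explore the effect of waiting that the Limitations section raises, but that is not app versus waiting.

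The 5% rejection rate follows from assuming equal app effects in both arms, so it illustrates the algebra and does not measure lost power in this trial. If the effects differed, the interaction would test that difference, which is still not app versus waiting. The article also does not say which term or effect size its 0.80 refers to. The fair criticism is that the figure has no stated derivation for any of these tests.

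A reader might further infer a loss of complete cases through missing T1 or T3 data. The article requires data only at baseline and 8 weeks for this cohort and does not say how the ANOVA treats other gaps, so no such loss can be established. Nor does correcting the visit labels require a move to all randomised participants; that is a preference.

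**Conclusion.** The layout is wrong as written and should be corrected, at the level of a sensitivity analysis. The arm and arm-by-time terms over T0 to T3 do not estimate app versus waiting list. This follows from the article's own visit definitions and conflicts with its own 8-week window. The size shown (about 5% rejection for both terms, and 24% to 38% for the arm term under a 0.2 SD drift) rests on assumed equal app effects, correlations of 0.3 to 0.7 and 64 per arm.

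The statement that every ANOVA has power 0.80 is unsupported: 80% is derived only for a two-group t test on one outcome. A reader might take this to undermine the primary comparison or the sample size. It does not: 184 reproduces exactly and does not depend on the ANOVA.

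The 24-week course for arm B is inferred from the text. Figure 1 is not available, and the Results section says 16 weeks. If 16 were right, arm B would have no visit 8 weeks after its active period, and the four-level layout could not be filled for that arm.

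**What to change.** 1. For the between-arm part of the sensitivity analysis, use arm A T0 and T2 against arm B T–1 and T0. Test arm-by-time or, preferably, fit an ANCOVA of the week-8 value adjusted for baseline. The per-protocol cohort can stay.
2. Keep T0 to T3 only as a pooled within-subject analysis, labelled as uncontrolled.
3. Delete the sentence giving all ANOVAs 0.80 power. Alternatively, restrict it to the QOLIE-10-P week-8 two-group comparison and state d, the number per arm and, for a change-score or arm-by-time test, the assumed baseline to week-8 correlation.
4. Reconcile the 16 weeks given for arm B in the Results section with the 24 weeks implied by Outcomes and Variables and Study Procedure.

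The cost is analysis wording and code. The visits needed are already in the schedule, so no new data are required and the sample size does not change.

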### Aims of This Study

In this exploratory randomized controlled trial (RCT), we will evaluate whether an 8-week CBT-based intervention, delivered through ThinkNinja for Epilepsy (Healios Ltd), is a clinically effective tool for improving the quality of life, mental health, and emotional well-being in a large sample of people with epilepsy.

We hypothesize the following:

There will be an improvement in participants’ self-reported quality of life scores, as measured by the 10-item patient-weighted Quality of Life in Epilepsy questionnaire (QOLIE-10-P) [28], as a result of the ThinkNinja for Epilepsy intervention.There will be an improvement in participants’ self-reported anxiety, depression, impression of change, and medication adherence, as measured by the 7-item Generalized Anxiety Disorder assessment (GAD-7) [29], the 9-item Patient Health Questionnaire (PHQ-9) [30], the Patient Global Impression of Change questionnaire (PGIC) [31], and the Medication Adherence Questionnaire (MAQ) [32], respectively, as a result of the ThinkNinja for Epilepsy intervention.There will be a positive association between the level of engagement with the app and the primary and secondary outcomes.

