Usage data to determine fidelity of the intervention and how closely the participants complied with the recommended guidance, covering which elements of the app they use the most and for how long they use different elements of the app.Goal-based achievement for those participants who set goals.Mood and anxiety scores and activity ratings throughout the study.Skill practice implementation data.

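### For anxiety and depression change, no named analysis keeps both engagement and outcome continuous, although the third hypothesis concerns the level of engagement

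*Protocol article*

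**What the plan says.** All references are to the protocol article.

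- **Aims of This Study**, third hypothesis: "There will be a positive association between the level of engagement with the app and the primary and secondary outcomes". This is a statement about level, and it covers the secondary outcomes as well as quality of life.
- **Outcomes and Variables**, list of measures captured within the app: usage data are logged, "covering which elements of the app they use the most and for how long they use different elements of the app".
- **Data Analysis**, under the lead-in "Further exploratory subgroup analyses will be performed for the following", the last bullet reads "Engagement variables: low versus high frequency and duration of app use". No cut point is given. The bullet before it has outcome change stratified by use of the app, of videoconferencing and of text support.
- **Data Analysis**, other uses of app data: the primary outcome is analysed "both unadjusted and adjusted for baseline characteristics, app use, and app content variables"; "Responder and nonresponder groups will be identified on the basis of changes in primary and secondary outcomes", after which "these groups will be characterized in terms of baseline characteristics, demographics, and app use variables" and a regression on responder status follows; and in the SEM "app use and content variables will be mediating latent variables, and quality of life will be the dependent variable".

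The article does not say which of these analyses tests the third hypothesis.

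**The concern.** A hypothesis about the level of engagement is best served by a measure that keeps the level. Here the app records use more finely than in two classes, but the analysis set out for engagement reduces it to two. That treats everyone on the same side of the cut as equally engaged and discards the gradient that the hypothesis is about. What is at stake is precision and power for one of the three stated hypotheses, chiefly for the anxiety and depression scores, where the other named analyses do not fill the gap.

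**Working it through.** **1. The plan's own figure, to fix the available N.** Sample Size gives a two-sided t test at 0.05, power 80%, d = 0.5, 30% dropout and 184 recruited. The t test needs 63.8, so 64 per arm; 64 / 0.70 = 91.4, so 92 per arm and 184 in total. The figure reproduces exactly. The engagement analyses could rest on 184 (all randomized, with imputation), about 129 (184 × 0.70 = 128.8) or 92 (one arm). The article gives no power figure for the low/high contrast.

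**2. What each named analysis does with engagement and outcome.**

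| Analysis (Data Analysis section) | Engagement | Outcome |
|---|---|---|
| Low/high contrast | two groups | not named in the bullet |
| Stratified by use | strata | change in primary and secondary outcomes |
| Responder characterization and regression | no split stated | responder or not |
| SEM | latent mediator, no split stated | quality of life only |
| Adjusted primary analysis | covariate, no split stated | quality of life only |

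For GAD-7 and PHQ-9 change, only the first three rows can apply. Two group the engagement variable and the third groups the outcome.

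**3. Information kept by a split.** Relative to a linear analysis of the continuous score X, a two-group version D keeps corr(X, D)². For normal X with a fraction p above the cut c this is φ(c)² / [p(1 − p)]. At the median, φ(0) = 0.3989, so 0.3989² / 0.25 = 0.637 = 2/π. The loss is 36.3%, and a correlation shrinks by √0.637 = 0.798. Effective N falls from 184 to 117, from 129 to 82, or from 92 to 59.

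**4. Effect on power (Fisher z, two-sided 0.05).** The correlation with 80% power on the continuous scale is r = tanh[(1.960 + 0.842) / √(N − 3)]. After the split, power is Φ[atanh(0.798 r) √(N − 3) − 1.960]. For N = 129: √126 = 11.22, r = 0.245, 0.798 r = 0.195, and power = Φ(0.26) = 0.60.

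| N | r with 80% power, continuous | Power after median split |
|---|---|---|
| 184 | 0.205 | 0.604 |
| 129 | 0.245 | 0.602 |
| 92 | 0.289 | 0.599 |

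The fall from 80% to about 60% hardly depends on which N applies.

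**5. How the loss depends on what is not stated.**

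| Assumed score and cut | Loss |
|---|---|
| Uniform, median | 25% |
| Normal, median | 36% |
| Normal, 33/67 | 41% |
| Normal, 25/75 | 46% |
| Normal, 20/80 | 51% |
| Gamma (shape 2), median | 45% |
| Exponential, median | 52% |
| Lognormal (sigma 1), median | 73% |

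The skewed rows come from simulation and assume that the outcome is linear in raw use. If it is linear in log use, a median split of a lognormal score loses the normal 36%, because the two groups are the same. Skew does not always make matters worse: with the cut at the upper quartile, the exponential and gamma scores each lose about 36%.

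**The case against.** The strongest reply is that the low/high contrast is one bullet among exploratory subgroup analyses in a trial that calls itself exploratory. App use also enters the SEM, the responder analysis and the adjusted primary analysis, and none of these is said to be split. The SEM path from app use to quality of life is itself an engagement–outcome association, reported with a confidence interval. This stands. A reader might infer that the plan reduces every test of engagement to two groups; the document does not say so. The reply falls short on the secondary outcomes, which the SEM does not cover. Nor does the adjusted primary analysis help there: it concerns quality of life, and in the first 8 weeks the waiting-list arm has no app, so use is bound up with arm.

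Three further inferences are tempting and unsupported.

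- **That the cut will be chosen after seeing the data, raising the false-positive rate.** The article is silent on how and when the cut is set, and an analysis plan that is not shown may fix it. Study Procedure gives a recommended frequency of use that could serve as a cut set in advance. A prespecified cut still loses information, so the point does not need this claim.
- **That power drops to 43%.** That figure, at n = 128, is for engagement and response both split at the median and crossed. The plan describes no such cross-classification.
- **That the SEM's stated power of 70.5% shows it cannot compensate.** That figure is for the 11-parameter model as a whole at N = 184. No power is stated for any single path.

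**Conclusion.** The point holds in limited form. The stated analysis of engagement is a two-group contrast, the third hypothesis concerns level, and no named analysis explicitly keeps both engagement and outcome continuous for GAD-7 and PHQ-9 change. For quality of life the SEM goes some way to cover the gap.

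The size is a loss of about 36% of the information, with 80% power falling to about 60%, if the score is normal, the relation linear and the cut at the median. A reader might take a loss of about a third as a property of the plan. It is not: neither the distribution nor the cut is in the document, and a range from about 25% to 50% or more is the fair statement. The absence of a cut point from the article is not itself a finding. The weakness is confined to an exploratory analysis and does not touch the randomized comparison of the primary outcome.

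**What to change.** For the third hypothesis, state that frequency and duration of app use are analysed as continuous variables, with a log or spline term if they are skewed. Set them against the continuous outcome score adjusted for its baseline value, for quality of life and for GAD-7 and PHQ-9, among participants with app access. Name this as the analysis that addresses the hypothesis, and keep the low/high and responder tables as description.

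The cost is a change of wording in the analysis section. Use is already tracked by the app, so there is no new data collection and no change to the sample size.

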### Sample Size

A formal sample size calculation was based on assumptions of QOLIE-10-P means and SDs from earlier studies [37,38]. It was performed using a 2-tailed *t* test of equal means at a significance level of .05 and a power of 80% for an estimated medium effect size (Cohen *d*=0.5). All calculations were done using the software nQuery (version 7.0; Statsols) [39]. We intend to recruit 184 people—92 participants in each arm—so that we can accommodate a dropout rate of 30%.

The chi-square method was used to determine the power for structural equation modeling (SEM) [40] using the associated online power calculator [41]. It was determined that with a sample size of 184 (see above) and a *P* value of .05, the proposed 11-parameter SEM analysis would be powered at 0.705 (70.5%).

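### The exploratory search for predictors of response regresses on a responder/nonresponder split of score changes, which costs information mainly for GAD-7 and PHQ-9 (minor)

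*Protocol article*

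**What the plan says.** The Data Analysis section of the protocol article sets out two linked steps. First, "Responder and nonresponder groups will be identified on the basis of changes in primary and secondary outcomes". Then, after a description of the two groups, "a regression model will be performed to identify variables associated with responder status". The article gives no cut-off and no expected share of responders.

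Other analyses in the same section keep the scores uncut:

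- **Primary analysis.** "We will be comparing changes in quality of life (ie, QOLIE-10-P scores) from baseline to completion of the 8-week program". It is run unadjusted and also adjusted for baseline characteristics, app use and app content.
- **Structural equation model (SEM).** Baseline characteristics are the independent variables, "app use and content variables will be mediating latent variables, and quality of life will be the dependent variable". No split of quality of life is mentioned.
- **Exploratory subgroup analyses.** One set is by baseline characteristics and demographics. Another is described as "Change in primary and secondary outcomes stratified by app use, videoconference use, and text support use".

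For anxiety and depression there is also a responder-type summary: "An analysis of reliable and clinical change will be produced for the GAD-7 and PHQ-9 scores". The text does not link it to the responder groups used in the regression.

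**The concern.** QOLIE-10-P, GAD-7 and PHQ-9 are numeric scores. Once a change in such a score is reduced to responder or nonresponder, a participant just short of the cut counts the same as one who got worse, and a participant just past it counts the same as the one with the largest gain. A regression on that binary variable has less power to detect predictors than one on the score. Which predictors emerge can also depend on where the cut is placed.

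Finding out who benefits is a declared aim. The third hypothesis under Aims of This Study links app engagement to the primary and secondary outcomes, and the Conclusions say that the analysis of engagement and outcome factors will inform later research and app development. The sample size was set for a two-arm comparison, not for this regression. A genuine association with anxiety or depression could therefore go undetected because of the coding of the outcome.

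**Working it through.** **Inputs from the protocol (Sample Size, Data Analysis)**

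- Two-sided alpha 0.05, power 80%, d = 0.5, 30% dropout, 184 participants (92 per arm).
- Analysis set for this regression: all randomised participants, with missing T2 values imputed.

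**Assumptions not in the protocol**

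- The share of responders, p.
- A normally distributed score, cut once.
- The strength of the predictor.

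**Step 1. Reproduce the planned sample size.** A two-sample t test with d = 0.5 needs 63.8, so 64 per arm. Allowing for dropout, 64 / 0.7 = 91.4, so 92 per arm and 184 in total. This matches the protocol. It says nothing about the responder regression, for which no power is stated.

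**Step 2. Information kept after the split.** For a normal score cut so that a share p respond, the asymptotic relative efficiency against the uncut score is

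ARE = φ(z_p)² / [p(1 − p)],

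where φ is the standard normal density and z_p the cut point. At p = 0.5: 0.3989² / 0.25 = 0.637. At p = 0.2: 0.2800² / 0.16 = 0.490. The result is the same for p and 1 − p.

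| Responder share | ARE | Loss | Equivalent N out of 184 | Equivalent N out of 128 |
|---|---|---|---|---|
| 50% | 0.637 | 36% | 117 | 81 |
| 30% | 0.576 | 42% | 106 | 74 |
| 20% | 0.490 | 51% | 90 | 63 |
| 10% | 0.342 | 66% | 63 | 44 |

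The last column uses 2 × 64 = 128, the number expected to provide T2 data after 30% dropout. It is shown because imputation does not restore the information lost to dropout.

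The 36% loss at an even split is the minimum under this model. The 51% is not a maximum.

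**Step 3. Check at a finite effect.** The formula is exact only for small effects. For a two-group predictor with d = 0.5, the uncut score needs 63 per group (normal approximation). The split score needs 100, 112, 134 and 200 per group at p = 50%, 30%, 20% and 10%. The losses, 1 − 63/n, are 37%, 44%, 53% and 69%, close to the table.

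**Step 4. Check by simulation.** A predictor correlated 0.207 with the score has about 80% power in linear regression at N = 184 (78% to 82% across runs of 1,500 replicates). Logistic regression on the split score has about 62%, 57%, 50% and 37% power at the same four shares.

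**Step 5. Which scales have another multivariable model on the uncut score?**

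| Scale | Analyses of the uncut score stated in Data Analysis |
|---|---|
| QOLIE-10-P | Analysis of change adjusted for baseline characteristics, app use and content; SEM; stratified subgroup analyses |
| GAD-7, PHQ-9 | Analysis of change, with no adjustment stated; stratified subgroup analyses |

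The repeated-measures ANOVAs compare arms and time points, so they do not examine predictors. For GAD-7 and PHQ-9 the responder regression is thus the only joint predictor model described.

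**The case against.** The strongest case against the point has four parts.

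1. **The scores are not discarded by the plan.** The adjusted analysis of QOLIE-10-P change and the SEM use the same families of predictors, and the subgroup analyses cover change in GAD-7 and PHQ-9. This stands for quality of life, where the information is largely kept. For GAD-7 and PHQ-9 it stands only in part, because stratified comparisons take one factor at a time and are not a joint model.

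2. **The percentages depend on a rule that the article does not give.** Responder status might follow reliable and clinical change, or a composite that includes the PGIC or MAQ, and the single-normal-score formula need not apply to either. This stands, so the figures can only be conditional. The undefined cut-off is not itself counted as a fault, since it may be set in an analysis plan that is not shown.

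3. **Describing who reaches a meaningful response is a legitimate question.** It differs from estimating score points per unit of a predictor. This stands as a reason to keep the responder groups for description. It is a weaker reason to make them the dependent variable in the search for predictors, because the groups can still be tabulated beside a continuous model.

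4. **The trial and this analysis are labelled exploratory.** This stands and limits the severity.

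A reader might infer that the plan as a whole loses 36% to 51% of its outcome information. The document does not support that. It gives neither a responder share nor a distribution, 51% is not an upper limit, and the loss falls on one regression only.

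**Conclusion.** The point holds as a minor one. The protocol does commit to a regression on responder status formed from outcome changes. If one roughly normal score is cut, the loss for that regression is at least about 36%, about 42% at a 30% share, about 51% at 20% or 80%, and about 66% at 10%. These figures rest on an assumed responder share and on normality, and the simulated powers also rest on an assumed correlation of 0.207.

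The practical consequence is mainly for GAD-7 and PHQ-9, where no multivariable model on the uncut score is stated. The primary comparison, the sample size and the secondary analyses of change are unaffected. It would also go too far to say that real predictors will be missed. The calculation shows only that power is lower than the same data would allow.

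**What to change.** Reword the predictor analysis in Data Analysis. At least for GAD-7 and PHQ-9, and preferably also for QOLIE-10-P, fit the regression to the continuous T2 score, with the same scale's pre-intervention baseline score as a covariate and the planned baseline and app-use variables as predictors. Keep the responder and nonresponder groups as a descriptive summary alongside the reliable and clinical change already planned for GAD-7 and PHQ-9.

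The change is to analysis wording only and needs no new data, visits or participants. The small downside is that coefficients are in score points rather than odds of response, which the descriptive responder table offsets. The PGIC and MAQ are outside this change. If they enter the responder definition, their role should be described separately.
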